## Abstract

**Electronic supplementary material:**

The online version of this article (10.1186/s40748-018-0093-1) contains supplementary material, which is available to authorized users.

## Introduction

### Scope of the problem

Persistent pulmonary hypertension of the newborn (PPHN) is a relatively common condition occurring in 0.5 to 7 per 1000 live births and results in a mortality ranging between 4 to 33% [1, 2]. Inhaled nitric oxide (iNO) and extracorporeal membrane oxygenation (ECMO) are the only current therapeutic options that are systematically evaluated in clinical trials [3, 4]. The vasodilatation induced by iNO is mediated by increasing concentrations of the second messengers: cyclic guanyl monophosphate (cGMP) and cyclic adenosine monophosphate (cAMP) in pulmonary vascular smooth muscle. The widespread use of iNO has resulted in a reduction in the need for ECMO; however, mortality and long-term morbidity remain unchanged [1, 4]. In addition, up to 40% of infants treated with iNO either have a transient response or fail to demonstrate an improvement in oxygenation [4, 5]. iNO does not improve myocardial performance in infants with PPHN, which often accompanies the condition and may contribute to mortality. Furthermore, the increasing cost of administering iNO to infants with PPHN may prohibit its use in developing countries. Due to these challenges, there is a real need to evaluate novel approaches to the management of PPHN.

### Pathophysiology and clinical characteristics of PPHN

The condition is clinically characterised by hypoxemic respiratory failure due to the lack of transition of the pulmonary vasculature from a high resistance fetal to a low resistance extra uterine circuit. Pulmonary vascular resistance (PVR) remains high resulting in right to left shunting across the patent foramen ovale (PFO) and the patent ductus arteriosus (PDA) resulting in hypoxemia. On a cellular level, the condition is characterised by marked endothelial dysfunction, with an excess of vasoconstrictor substances (phosphorylated myosin light chains (MLC-P), endothelin 1 (ET-1) and reactive nitrogen species) over vasodilator compounds (cGMP, cAMP, and myosin light chain phosphatase (MLCP)) [6, 7]. Chronic exposure to hypoxia may lead to pulmonary vessel wall thickening with increased connective tissue deposition and neo-muscularisation. This results in a more permanent vascular change termed pulmonary vascular remodelling [8].

### Myocardial dysfunction associated with PPHN

Right (RV) and left (LV) ventricular function may be compromised in PPHN as a result of increased RV afterload and reduced LV preload (due to the reduced pulmonary venous return) [9]. The effects of a pressure-loaded, dilated right heart include a shift in the interventricular septum and compression of the left ventricle, both resulting in decreased LV filling and hence cardiac LV output (LVO). The low cardiac output state resulting from reduced LV preload can lead to a fall in blood pressure in infants with PPHN necessitating the use of vasoactive inotropes such as dopamine and adrenaline. Animal data suggest that these inotropes raise systemic and pulmonary vascular resistance and may further contribute to RV compromise in the setting of PPHN [10, 11]. Several studies have demonstrated the association of a low cardiac output in the setting of PPHN with morbidity and mortality [12–14].

### The potential use of milrinone in PPHN

Cyclic nucleotide phosphodiesterases (PDE) are a family of enzymes that hydrolyse the phosphodiester bond in cAMP and cGMP thereby inhibiting their pulmonary vasodilator properties. Two isoforms, PDE3 and PDE5 are abundantly present in the neonatal lung and play a key role in the pathogenesis of PPHN [15]. PDE3 has a predominant hydrolysing effect on cAMP. Milrinone is a selective PDE3 inhibitor with pharmacological effects including relaxation of vascular smooth muscle, enhanced myocardial contractility (inotropy) and improved myocardial relaxation (lusitropy) [16, 17]. In the newborn lamb, intravenous milrinone augments the action of prostaglandins (PGI_2_) on pulmonary vasculature by significantly shortening the onset and prolonging the duration and degree of pulmonary vasodilation produced by PGI_2_ [18, 19]. Milrinone may also exhibit synergistic effects with iNO in lowering PVR [20, 21].

The use of milrinone is established in neonates and children following cardiac surgery for the prevention of low cardiac output syndrome and the treatment of pulmonary hypertension [22, 23]. Its use in the setting of PPHN of the newborn is limited to case series demonstrating an improvement in oxygenation when used in infants with PPHN failing to respond to iNO [24, 25]. Through its lusitropic and inotropic properties, milrinone may be an effective agent in addressing RV and LV dysfunction in the setting of PPHN.

### Lack of consensus in the management of PPHN

Despite recent advances in the management of PPHN, the risk of mortality and adverse neurological sequelae remains high and often prompt neonatologists to institute additional therapies. However, there is no consensus on the choice of therapeutic interventions in addition to iNO. Characterizing variation in practices is a crucial step toward improved patient outcome. As a result, our group conducted a prospective cross-sectional online survey of neonatologists to evaluate intensive care practices in Canada and the Australia-New Zealand region (AUS-NZ).

A 35-item questionnaire was developed, validated, and piloted to collect information on diagnosis, inhaled nitric oxide (iNO) practices, alternative vasodilators or cardiotropes, and echocardiography. Variation among survey respondents as well as intergroup comparison was performed. Data were collected from 217 respondents. Echocardiography and arterial blood gas were the most common diagnostic tests used to assess the severity of PPHN. iNO administration was more frequently scrutinized in Canada (36% versus 10% [AUS-NZ], *p* < 0.001) due to the higher cost of the therapy in North America. As a consequence, Canadian neonatologists reported higher use of intravenous milrinone (*p* < 0.001), vasopressin (*p* = 0.02), and inhaled prostacyclin (*p* = 0.02), but lower use of sildenafil (*p* = 0.01) for refractory pulmonary hypertension. A greater proportion of neonatologists in AUS-NZ were trained to perform echocardiography (*p* < 0.001) to optimize treatment decisions. As a result of this wide variation in the management of PPHN, there is a need to provide more guidance regarding principles of management while recognizing the dynamic nature of cardiopulmonary physiology in individual patients [26].

### Pharmacokinetics of milrinone in PPHN

The pharmacological profile of milrinone in persistent pulmonary hypertension of the newborn, its short term outcomes and safety profile was recently delineated by our group in an open label prospective pharmacological study of 11 neonates with PPHN [27]. The study included infants ≥34 weeks gestation with birth weights ≥1500 g; less than 10 days old and within 24 h of admission; echocardiography diagnosis of PPHN [right to left shunt at PFO or PDA level and/or severe tricuspid regurgitation]; absence of congenital heart disease and an indwelling arterial line. The most common reasons for PPHN were meconium aspiration syndrome and hypoxic-ischemic encephalopathy. The median ages at administration of iNO and milrinone were 7.5 h (range 4–22) and 14 h (range 10–30); therefore, the interval between these co-treatments was a median of 7 h (4.5–16). All patients required 100% oxygen prior to administration of iNO. There was no interval improvement in median oxygen requirement (100% vs. 98% [86–100], *p* = 0.35) or oxygenation index (37.2 ± 9.0 vs. 41.6 ± 21.6, *p* = 0.53) after iNO administration (prior to initiation of milrinone).

Infants received an intravenous loading dose of milrinone (50 μg/kg) over 60 min followed by a maintenance infusion (0.33–0.99 μg/kg/min) for 24–72 h. Serial blood milrinone levels were collected after the bolus, following initiation of the maintenance infusion to determine steady state levels, and following discontinuation of the drug to determine clearance. Echocardiography was performed before and after (1, 12 h) milrinone initiation. The mean (SD) gestational age and weight at birth were 39.2 ± 1.3 weeks and 3481 ± 603 g. The median dose and duration of milrinone following the bolus were 0.33 μg/kg/min (range 0.33–0.99 μg/kg/min) and 24 h (range 24 to 42 h). The mean (SD) half-life, total body clearance, volume of distribution, and steady state concentration of milrinone were 4.1 ± 1.1 h, 0.11 ± 0.01 L/kg/hour, 0.56 ± 0.19 L/kg, and 290.9 ± 77.7 ng/ml.

The initiation of milrinone led to an improvement in PaO_2_ (*p* = 0.002) and a sustained reduction in FiO_2_ (*p* < 0.001), oxygenation index (*p* < 0.001), mean airway pressure (*p* = 0.03), and inhaled nitric oxide dose (*p* < 0.001). Although a transient reduction in systolic arterial pressure (*p* < 0.001) was seen following the bolus, there was overall improvement in base deficit (*p* = 0.01) and plasma lactate (*p* = 0.04) with a trend towards lower inotrope score. Serial echocardiography revealed lower pulmonary artery pressure, improved right and left ventricular output, and reduced bidirectional or right-left shunting (*p* < 0.05) after milrinone treatment. No infants were withdrawn from the study and there were no cases of intraventricular haemorrhage, electrolyte disturbances, abnormal liver or coagulation profiles, thrombocytopenia, need for ECMO or mortality.

Milrinone administration was associated with an increase in LVO (*p* = 0.04), RVO (*p* = 0.004), RV strain (*p* = 0.01) and strain rate (*p* = 0.002), and LV s` (*p* < 0.001) and a` (*p* = 0.02) tissue Doppler velocity waves. There was a significant reduction in iNO dose, oxygen requirement over the subsequent 72 h (all *p* < 0.05). In addition, the administration of milrinone was associated with a reduction in mean blood pressure (*p* = 0.04) peaking at 6 h post administration. This was associated with a significant increase in the use of vasoactive inotropes at 6 and 24 h. However, blood pressure began to increase after 12 h of milrinone administration with a peak at 72 h (systolic BP *p* = 0.02, mean BP *p* = 0.03, diastolic BP *p* = 0.02) in spite of a reduction in the use of vasoactive inotropes over the same time period.

### Rationale for milrinone use

PPHN is common and leads to a major burden of neonatal illness, carries a significant mortality, need for ECMO, and adverse neurodevelopmental outcome. There is poor appreciation of the physiologic determinants of PPHN and predictors of iNO response at presentation; up to 40% of infants do not respond to iNO treatment. The increasing cost of iNO may preclude its use in both the developed and developing countries. The use of milrinone in infants with PPHN as an adjunct to iNO is worth further exploration with preliminary evidence suggesting an improvement in both oxygenation and myocardial performance in this group of infants. It’s inotropic, lusitropic and pulmonary vasodilator properties make it an ideal agent to use in this setting and may improve response to therapy and reduce mortality associated with the disease.

A recent Cochrane review illustrated the lack of randomised controlled trials (RCTs) comparing the use of milrinone versus placebo or as an adjunct to iNO compared with iNO alone in the setting of PPHN and recommended limiting the use of milrinone in PPHN to the research setting [29]. It is important to systematically investigate the efficacy of milrinone in the setting of PPHN prior to widespread dissemination of this treatment.

### Objectives

#### Primary objective

We hypothesize that intravenous milrinone used in conjunction with iNO results in the reduction in the time on iNO therapy and the time spent on invasive ventilation in infants ≥34 weeks gestation and ≥ 2000 g with a clinical and echocardiography diagnosis of PPHN.

#### Secondary objective

The aim is to compare: the incidence of the use of other inotropes; critically low LV and RV function and output measured by echocardiography and a non-invasive cardiac output monitor (NICOM); the rate of adverse effects associated with milrinone including the incidence of hypotension; and the pre-discharge outcomes in the two groups. In this pilot study, we aim to assess the practicality of instituting the protocol and contributing to a sample size calculation for a definitive multicentre study.

### Trial design

This is a multicentre, randomized, double-blind, two arm pilot study, with a balanced (1:1) allocation that will be carried out in the level III neonatal intensive care units in 2 centres in Ireland: The Rotunda Hospital Dublin and Cork University Maternity Hospital, and one centre in the Netherlands: Radboudumc Amalia Children’s Hospital, Nijmegen (Fig. 1).

**Fig. 1 Fig1:**
[figure not shown]
Trial Schematic

### The relevance of the primary outcome

iNO use is expensive and currently requires invasive ventilation. Invasive ventilation can cause baro- and volutrauma, may lead to parenchymal lung damage and the evolution of pneumothoraces. Ventilation is often accompanied by the administration of sedative agents such as morphine and midazolam. In addition, prolonged ventilation will delay bonding with parents, delay feeding and suckling and will lead to prolonged hospitalisation. A reduction in the time spent invasively ventilated will (in addition to the other benefits outlined above) reduce hospital stay, promote earlier enteral nutrition, parental bonding, breast feeding and significantly reduce healthcare costs.

The purpose of this pilot study is to assess the feasibility of performing a pivotal trial and to obtain preliminary data to calculate a sample size for a definitive multi-centre trial of milrinone therapy in PPHN. We aim to recruit a total of 20 infants with PPHN (10 receiving milrinone and 10 receiving placebo) over a 4-year period. We then plan to seek additional funding in order to facilitate the running of the multicentre RCT in European and North American centres. In this pilot study we also aim to ascertain issues with recruiting infants and obtaining consent, compliance with the protocol, the rate (if any) of loss to follow up, and the general acceptability, feasibility and compliance of administering the intervention. This number will also allow us to calculate a standard deviation which will be used in a sample size calculation for the full-scale trial. In addition, we aim to refine the criteria for discontinuing therapy which are outlined below.

## Methods

### Participants interventions and outcomes

#### Setting

This feasibility study will be conducted in three Level III neonatal intensive care units (NICU). Two in Ireland: The Rotunda Hospital, Dublin, and Cork University Maternity Hospital; and one in the Netherlands: Radboudumc Amalia Children’s Hospital, Nijmegen.

#### Eligibility criteria

All infants with a gestation ≥34 week and a birth weight ≥ 2000 g admitted to the neonatal intensive care unit with a clinical diagnosis of PPHN and commenced on iNO will be deemed potentially eligible for this study. The process of iNO initiation in PPHN on clinical grounds and is standardised in the NICUs and is detailed in Additional file 1. The decision is made by the attending physician. In addition; the infants must satisfy the following criteria:≤ 10 postnatal days of life and within 4 days of admissionEchocardiography diagnosis of PPHN (see below)Absence of significant congenital heart defect excluding a small atrial septal defect or ventricular septal defect (measuring less than 3 mm)Oxygenation index of ≥10 measured obtained from an arterial blood sample and calculated using the following formula: OI = (Mean airway pressure × FiO_2_ × 100) ÷ (paO_2_ in kilopascals)

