#### Monitoring, outcome measures and participant timeline

The primary outcome of this study is the time on iNO in hours and the time on invasive ventilation. A standardised protocol for iNO weaning is detailed in Additional file 2.

We will collect the following demographic characteristics and relevant short-term secondary outcomes: duration of hospital stay; time to extubation; duration of oxygen therapy, and survival.

**Details of cardiorespiratory stability** (blood pressure, heart rate, oxygen saturation), ventilation support (FiO_2_, mean airway pressure (MAP), oxygenation index [MAP × F FiO_2_/PaO_2_]), efficacy of oxygenation [PaO_2_], plasma lactate, pH, PCO_2_, HCO_3_^−^, Base excess; and relevant co-treatments (i.e., sedation, analgesics, muscle relaxants, inotropes, fluid administration) at the following time points:Prior to treatmentFollowing the loading dose12 h after initiation of therapy24 h after initiation of therapyTwo hours after discontinuation of therapy

**Monitoring of blood parameters** will be carried out as follows during the study period and 24 h after drug discontinuation:Full blood count (including platelets): dailyElectrolytes, Urea and Creatinine: dailyLiver function tests (ALT, AST, GGT): dailyBlood gas analysis: 12 hourly

**Echocardiography** will be performed according to the following schedule: a timing window of ±3 h will be applied. Scans performed outside the ±3 h window will constitute a protocol deviation:Prior to the Commencement of Study Drug: Diagnose PPHN and rule out CHD12 h following the administration of Study Drug24 h following the administration of the study drug8 h following the discontinuation of the study drug

**Non-invasive Cardiac output Monitoring (NICOM)** will be commenced prior to the commencement of the study drug and continued until the last echocardiogram, 8 h after the discontinuation of the study medication.

**Cranial ultrasound** will performed prior to treatment commencement and after the discontinuation of the infusion. Intraventricular haemorrhage will be defined and graded with the Papile classification [30]. Echocardiography will be carried out at baseline as detailed above and at 12 h, 24 h, 2 h after discontinuation of therapy, and before discharge.

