#### Recruitment strategies

The recent incidence of pulmonary hypertension in the three study sites is 1–2 per 1000 live births. The total annual birth rate in the 3 centres is around 24,000 giving 24–48 potential eligible infants. The rate of moderate to severe PH in this cohort (fulfilling the eligibility criteria) will be around 50% (12–24 infants per annum). We anticipate a 50% to 75% enrolment rate per year to account for consent refusal, competition with other studies and unavailability of staff to recruit patients. Therefore, we anticipate a recruitment period of 4 years. All centres are experienced in the conduct of clinical trials. They also have the expertise to carry out the assessment of the primary and secondary outcomes and to perform the echocardiography and NICOM assessments. We do not anticipate any variability in administering the intervention between sites over time.

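### The oxygenation-index cut-off of 10 is paired with PaO2 in kilopascals; it equals only 1.33 with PaO2 in mmHg, so the criterion is almost inert in infants on iNO

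*Protocol article*

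**What the plan says.** - **Entry rule.** In the protocol article, Eligibility criteria, one condition is "Oxygenation index of ≥10 measured obtained from an arterial blood sample". The formula beside it is "OI = (Mean airway pressure × FiO_2_ × 100) ÷ (paO_2_ in kilopascals". The PaO2 unit is spelled out; the MAP unit is not given. The rule applies to infants "with a clinical diagnosis of PPHN and commenced on iNO will be deemed potentially eligible".
- **Follow-up index.** Monitoring, outcome measures and participant timeline defines the index again as "oxygenation index [MAP × F FiO_2_/PaO_2", without the factor 100 and without any unit.
- **The group's earlier data.** Pharmacokinetics of milrinone in PPHN reports, before and after iNO, "oxygenation index (37.2 ± 9.0 vs. 41.6 ± 21.6, *p* = 0.53", and states that "All patients required 100% oxygen prior to administration of iNO".
- **Recruitment forecast.** Recruitment strategies assumes: "The rate of moderate to severe PH in this cohort (fulfilling the eligibility criteria) will be around 50" per cent, which it counts as 12–24 infants a year out of 24–48.

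No section converts the unit or rescales the cut-off.

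**The concern.** An OI has no meaning apart from the units that go into it. With PaO2 in kilopascals the denominator is 7.5 times smaller than in mmHg, and every score is 7.5 times larger. If the cut-off of 10 was chosen on the mmHg scale, the printed rule sets a far lower bar than intended.

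The OI is the only numerical oxygenation threshold among the entry criteria, so it is the natural place for disease severity to be fixed. The section on the relevance of the primary outcome says that the pilot will supply the standard deviation and the feasibility data for the definitive trial. Both should describe a clearly defined population. Three sites in two countries could also apply the rule differently, some as printed and some silently corrected.

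**Working it through.** **Figures the article derives.** The recruitment numbers reproduce: 24,000 × 1/1000 = 24 and 24,000 × 2/1000 = 48; half of these is 12 and 24. The cut-off of 10 is not derived anywhere, so there is no calculation behind it to reproduce.

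**Step 1: unit conversion.** 1 kPa = 7.5 mmHg.
- A cut-off of 10 with PaO2 in kPa equals 10 / 7.5 = 1.33 with PaO2 in mmHg.
- A cut-off of 10 with PaO2 in mmHg equals 10 × 7.5 = 75 on the printed formula.

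**Step 2: which scale do the group's own values use?** Rearranged, PaO2 = MAP × FiO2 × 100 / OI. From the earlier study, OI = 37.2 and FiO2 = 1.0. MAP is not reported, so 10–25 cmH2O is assumed.

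| Assumed MAP | 100 × MAP / 37.2 | If OI is on the mmHg scale | If OI is on the kPa scale |
|---|---|---|---|
| 10 | 26.9 | 27 mmHg (3.6 kPa) | 27 kPa (202 mmHg) |
| 15 | 40.3 | 40 mmHg (5.4 kPa) | 40 kPa (302 mmHg) |
| 20 | 53.8 | 54 mmHg (7.2 kPa) | 54 kPa (403 mmHg) |
| 25 | 67.2 | 67 mmHg (9.0 kPa) | 67 kPa (504 mmHg) |

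A PaO2 of 202–504 mmHg does not fit hypoxaemic infants who need 100% oxygen; 27–67 mmHg does. The earlier values are therefore on the mmHg scale. By the formula in Eligibility criteria, the same mean would be 37.2 × 7.5 = 279.

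**Step 3: whom does the printed rule exclude?** An infant fails only if PaO2 exceeds MAP × FiO2 × 10 kPa. PaO2 cannot exceed alveolar oxygen pressure. This is bounded by the alveolar gas equation, with assumed barometric pressure 101.3 kPa, water vapour 6.3 kPa, PaCO2 5.3 kPa and R = 0.8:
- FiO2 below 1: maximum = FiO2 × 95 − 5.3 / 0.8.
- FiO2 of 1: maximum = 95 − 5.3.

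The MAP above which the OI is at least 10 whatever the lung function is that maximum divided by (10 × FiO2).

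| FiO2 | Maximum PaO2 (kPa) | No infant can fail above MAP (cmH2O) |
|---|---|---|
| 0.21 | 13.3 | 6.4 |
| 0.40 | 31.4 | 7.8 |
| 0.50 | 40.9 | 8.2 |
| 1.00 | 89.7 | 9.0 |

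The result depends little on PaCO2: even at a PaCO2 of zero the bound is only 95 / 10 = 9.5 cmH2O.

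**Step 4: examples.**
- MAP 10, FiO2 0.5, PaO2 10 kPa: 10 × 0.5 × 100 / 10 = 50 as printed; 50 / 7.5 = 6.7 on the mmHg scale.
- MAP 8, FiO2 0.4, PaO2 10 kPa: 32 as printed; 4.3 on the mmHg scale.
- MAP 5, FiO2 0.21, PaO2 12 kPa: 105 / 12 = 8.8 as printed, which fails.

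The first two pass as printed and would not pass a cut-off of 10 on the mmHg scale. The third shows that an infant on minimal support can still fail.

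**The case against.** **The other criteria do the selecting.** Candidates must already be on iNO, meet an echocardiographic definition, satisfy the gestation and weight limits and clear the exclusions. iNO initiation is described as standardised in Additional file 1, which is not shown. This stands. A reader might infer that the trial selects nobody out, or that all 24–48 infants a year become eligible. The documents do not support either reading: the 24–48 are all infants with pulmonary hypertension, and the forecast of one half refers to the eligibility criteria together, not to the OI alone.

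**The cut-off may hardly bind on either scale.** In the earlier study 10 lies (37.2 − 10) / 9.0 = 3.0 SD below the pre-iNO mean and (41.6 − 10) / 21.6 = 1.5 SD below the later one. Under rough normality about 0.1% and 7% of such infants would fall below it. That study had 11 infants, all of whom went on to milrinone, so it is a weak guide to the trial population. It is still enough to bar the inference that mild cases will dilute the effect by some known amount.

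**The MAP unit might rescue the formula.** With MAP also in kPa, the index would be about 0.74 times the usual value and the discrepancy would largely vanish. Nothing in the text says so.

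**It may be a printing slip.** Sites may use mmHg in practice. The article does not show this, and the printed text would remain wrong.

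**The follow-up formula need not conflict.** The article often writes FiO2 as a percentage, and then the factor 100 is already included. A reader might infer a further, different scale for the follow-up index; this is not shown. What is shown is that its units are undefined.

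**Both arms face the same entry rule.** This is true, so the randomised comparison is not biased. The issue is who is enrolled and how they are described.

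**Conclusion.** The point holds for the OI criterion itself. As printed, the cut-off and the PaO2 unit disagree by a factor of 7.5 when set against the group's own OI values. The threshold is equivalent to 1.33 on the mmHg scale. Among infants ventilated on iNO it excludes none above a MAP of about 9 cmH2O, and below that only infants with good oxygenation on little support. It cannot contribute to the moderate-to-severe selection assumed in Recruitment strategies.

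This rests on MAP in cmH2O, on an assumed MAP of 10–25 cmH2O in the earlier study, and on standard values in the alveolar gas equation. The scale conclusion is the same across the whole assumed MAP range.

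The size of any change in the enrolled population, in the standard deviation carried forward or in the recruitment rate cannot be worked out from the document, and no such figure is claimed. A numerical entry threshold that is wrong as written should nonetheless be corrected.

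**What to change.** 1. State which PaO2 unit and which MAP unit the cut-off of 10 belongs to.
2. Make formula, unit and cut-off agree in Eligibility criteria. If the mmHg scale was meant, as the earlier study's values imply, give PaO2 in mmHg or multiply kPa by 7.5 in the denominator.
3. In Monitoring, outcome measures and participant timeline, use the same formula and units for the follow-up index, and say whether FiO2 is a fraction or a percentage.
4. Recompute the entry index of any infant already enrolled from the recorded MAP, FiO2 and PaO2, and report it on the stated scale.

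The cost is a short amendment and a change to the formula on the data collection sheet. The downside, if the mmHg scale was meant, is that fewer infants qualify than under the literal formula. The recruitment forecast already assumes that only about half of cases meet the criteria as a whole.
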